#### *The Numeric Rating Scale (NRS):*

The NRS is a discontinuous, self-report measure. It consists of a single item, in which the respondent is asked to rate the intensity of pain. This rate is done on an 11-point scale ranging from 0-10, anchored by verbal descriptors at either end of the scale. In the context of pain, the NRS has been proven to have good reliability and validity (Hawker, Mian, Kendzerska, & French, 2011; Johnson, 2005). It is a valid measure of pain intensity (0-10) that is less influenced by present mood state (54), and has been widely used to assess post-surgical pain in previous studies of women with breast cancer (3, 7, 8, 55).

#### *The Visual Analog Scale (VAS):*

The VAS is a continuous, self-report measure comprised of either a horizontal or vertical line measured at exactly 100 mm. The line is anchored by verbal descriptors, and the respondent is asked to rate the intensity of their symptom by making a mark on the line. The distance between the end of the line, representing absence of the symptom, and the mark will be measured and a score ranging from 0 to 100 will be recorded. Similar to the NRS, the VAS can be used on a variety of symptoms and will here be used to assess fatigue and muscle weakness (Hawker et al., 2011; Johnson, 2005).

#### *The Surgical Fear Questionnaire (SFQ):*

The SFQ is a reliable and valid self-report instrument designed to assess fear of surgery, and it consists of 8 items which is scored on an 11-point scale ranging from 0 (not at all afraid) to 10 (very afraid). The items target different fears concerning surgery, namely fear of operation, anaesthesia, postoperative pain, side effects, health deterioration, failed operation, incomplete recovery and long duration of rehabilitation. The structure of the SFQ can best be described by a two-factor model, in which two subscales can be distinguished: fear of immediate consequences of surgery and fear of the long-term consequences (Theunissen et al., 2014).

#### *Life Orientation Test – Revised (LOT-R)*

The LOT-R is a 10 item self-report test meant to assess dispositional optimism. The respondents are asked to rate their agreement to various statements on a 5-point scale ranging from 0 (strongly disagree) to 4 (strongly agree). Three of the items assess optimism, three assess pessimism, and the remaining four are filler items that are not meant to be included in the scoring (Hinz et al., 2017).

### *Hospital Anxiety and Depression Scale (HADS)*

The HADS is a scale specifically designed for patients with physical illness, and it makes no references to somatic symptoms such as fatigue, insomnia or headache. It is a self-administered rating scale comprised of 14 items that are equally divided into two subscales: depression and anxiety. Each subscale therefore consists of seven items, and the respondents are asked to respond on a 4-point scale ranging from 0 to 3. Consequently, each subscale has a possible score of 0-21, and a score of 11 or higher often indicates problematic presence of either depressive or anxious symptoms (Bjelland, Dahl, Haug, & Neckelmann, 2002; Carroll, Kathol, Noyes, Wald, & Clamon, 1993; Snaith, 2003; Zigmond & Snaith, 1983).

### *The Pain Catastrophizing Scale (PCS)*

The PCS is a self-report measure meant to assess catastrophizing. It is comprised of 13 items, each rated on a 5-point scale ranging from 0 to 4 (A. Osman et al., 2000; Augustine Osman et al., 1997; Sullivan, Bishop, & Pivik, 1995).

### *The 13-item Functional Assessment of Chronic Illness Therapy-Fatigue subscale (FACIT-F)*

The FACIT-F is a unidimensional self-report scale meant to assess fatigue and its impact on daily life. Consisting of 13 items, the scale asks the respondents to rate their level of symptom intensity on a 5-point scale ranging from 0 to 4 (Butt et al., 2013; Yellen, Cella, Webster, Blendowski, & Kaplan, 1997). FACIT-F is a widely used measure of fatigue in breast cancer trials. It has demonstrated excellent internal consistency, high validity, and sensitivity to pick up change in patients with breast cancer (51).

### *Insomnia Severity Index (ISI)*

The ISI is a 7-item instrument, measuring severity, nature and impact of insomnia symptoms. It is a brief screening and outcome measure for use in treatment research, and the scale corresponds in part to DSM-IV criteria for insomnia. The respondents are asked to rate their symptoms on a 5-point scale ranging from 0 to 4, which assess the subject's current perception of symptom severity, distress and impairment (Morin, Belleville, Bédard, & Ivers, 2011; Smith & Wegener, 2003).

*The European Organization for Research and Treatment-QOL questionnaire for breast cancer specific module (EORTC QLQ-BR23)*

The EORTC QLQ-BR23 is a health-related quality of life measure specifically designed for women with breast cancer. It consists of 23 items, each asking the respondent to indicate the extent to which they have experienced certain symptoms or problems on a 4-point scale ranging from "not at all" to "very much" (Nguyen et al., 2015; Sprangers et al., 1996). This measure was specifically included upon recommendation from our user representative.

*Injustice Experience Questionnaire (IEQ)*

The IEQ is a 12-item measure meant to assess the respondent's experience of injustice. Injustice encompasses the degree of blame as well as the magnitude and irreparability of loss related to their health condition. The items therefore consists of thoughts and feelings related to injustice. Respondents are asked to rate their experience of injustice on a 5-point scale ranging from "not at all" to "all the time" (Sullivan et al., 2008). The scale was originally developed for patients with chronic pain conditions, but will in the current study be slightly adjusted to apply to patients diagnosed with breast cancer.

*Eysenck Personality Questionnaire Revised for Neuroticism (EPQ-R Neuroticism)*

The EPQR for Neuroticism is a measure meant to assess neuroticism, defined as a quantitative personality trait believed to predict an individual's vulnerability to neurotic disorders (Birley et al., 2006). There are several versions of the EPQR, each with satisfactory reliability and validity. Usually an EPQR involves other traits as well, but in this study only a 12-item EPQR for neuroticism will be used. Hence, the other traits will be excluded, and only neuroticism will be measured. As with most EPQRs the respondents will be asked to answer either "yes" or "no" on various statements regarding neuroticism and emotional stability (Francis & Pearson, 1988).

### *Blood analyses*

The immune functional assay will consist in collecting whole blood samples using the standardized TruCulture system (Myriad RBM, Austin, Texas, USA) directly containing immunogenic stimuli: medium alone (Null), LPS at 100 ng/mL (from *Escherichia coli* O55:B5), and *Staphylococcus aureus* enterotoxin B (SEB) at 0.4 µg/mL, respectively. Immune function is assessed by the commercially available test TruCulture® (Myriad RBM, Austin, USA). TruCulture® reproducibly reveals the induced innate and adaptive immune response in whole blood after stimulation, by quantifying the release of soluble immune activation products (cytokines, chemokines, soluble receptors etc.) in the supernatant and by measuring the transcription level (mRNA) in the circulating blood (immune) cells (53).

### **Data collection and management**

Self-reported data and biomarker data will be collected pre-surgery (questionnaires, hair and blood), post-surgery upon discharge (brief phone survey), 3-4 weeks after surgery (blood), as well as 3 and 6 months after surgery (only questionnaire data). These time points either align with clinical follow-ups at the outpatient oncology department, or are responded to through an

electronic link in the patients' homes to avoid unnecessary strain on the patient. Patient charts will be used to collect data on surgical procedures and potential complications during/after surgery. This will include information about the duration of the surgery, tumor-related variables, severity of acute post-surgical pain, and other relevant intra-operative variables. Registry data on employment and benefit take-up and medical prescriptions will be obtained from FD-Trygd and the Norwegian Prescription Database (NorPD), respectively. To be able to assess for the effects of the interventions, data from NorPD and FD-Trygd will be obtained from inclusion in the trial until one year follow-up. The NorPD contains data about dispensed drugs in Norway, while FD-Trygd contains social security micro data for research. These data will be obtained retrospectively. The post-operative booklet that the patients receive as part of the iACT will also be collected at 6 months follow-up to assess if the patients used it as intended.

----- INSERT FIGURE 1-----

Survey data will be collected electronically by the use of laptops/smartphones. We will also utilize data from patients' medical records regarding surgical procedures and medical variables, as well as registry data, which will be linked to the survey data. Data from medical records as well as test results from blood samples will be entered directly into Viedoc by our study nurse. All data will be stored on a secure server at the hospital. The hospital already have a system in place for secure collection and storing of sensitive data which will be used.

A detailed plan for data management and sharing will be developed in collaboration with both Oslo University and the University of Oslo that shares the responsibility for data management in this study.

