## Abstract

**Background:** Breast cancer is the most common cancer type among women with >1million new cases worldwide. More than 40% of them will struggle with pain and fatigue years after surgery, regardless of surgical procedure. These consequences are detrimental and result in distress and disability, including work disability. Few previous attempts have been made to prevent persistent pain and fatigue after surgery by applying a psychological approach, despite psychological risk factors being crucial in the development of both persistent pain and fatigue. In this study, we aim to develop and test an easily implementable strategy of preventing persistent pain and fatigue after breast cancer surgery. The intervention strategy involves a pre-operative hypnosis session and a web-based post-operative Acceptance and Commitment Therapy. The hypnosis was previously found effective in alleviating acute post-operative pain and fatigue in breast cancer patients, while ACT may be particularly well suited to cancer populations as it offers a model of healthy adaptation to difficult circumstances. Together they form an intervention strategy with both a preventive and a rehabilitative focus.

**Methods/design:** The study will be run as a randomized controlled trial where effects of the pre- and post- operative interventions will be compared to attentional control and treatment as usual (TAU). Patients will be randomized to receive either a brief hypnosis session before surgery, and a web-based psychological intervention after surgery (ACT), or mindfulness meditation administered through a mobile app before surgery and TAU after surgery. Measurement, in the form of self-reported data and biomarker data will be assessed pre-surgery, post-surgery and 3 and 6 months after surgery.

**Discussion:** This study will be the first study to combine a pre-operative hypnosis with a post-operative ACT to prevent pain and fatigue after breast cancer surgery. The results from our study might i) help the large group of women affected by chronic pain and fatigue after breast

cancer surgery, ii) shed light on the mechanisms involved in chronic pain development, and  
iii) serve as a model for other surgical procedures.

**Trial registration:** The project will be registered in a relevant international trial register.

**Keywords:** Breast cancer; pain; post-surgical pain; fatigue; hypnosis; acceptance and  
commitment therapy

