## **Methods/Design**

### **Aims and objectives**

The primary aim of the study is to develop and test an easily implementable strategy of preventing persistent pain and fatigue after breast cancer surgery. The intervention strategy involves a pre-operative hypnosis session and a post-operative, internet-based Acceptance and Commitment Therapy (iACT). The hypnosis was previously found effective in alleviating acute post-operative pain and fatigue in breast cancer patients, while ACT may be particularly well suited to cancer populations as it offers a model of healthy adaptation to difficult circumstances. Together they form an intervention strategy with both a preventive and a rehabilitative focus.

We have the following hypotheses:

- 1) Hypnosis is more effective than one-session mindfulness in relieving acute post-surgical pain and fatigue
- 2) Hypnosis alters markers of bodily stress responses and impacts immune reactivity associated with pain and fatigue.
- 3) Hypnosis + iACT results in less post-surgical pain and fatigue and fewer medical prescriptions for pain medication 3 months after surgery compared to one-session mindfulness + TAU

- 4) Hypnosis + iACT is favorable in a cost-utility analysis, and will result in fewer days of sick leave at 1 year follow-up compared to one-session mindfulness + TAU
- 5) Hypnosis + iACT results in less psychological distress and fewer medical prescriptions for psychotropic medications at the 3 and 6-month follow-ups compared to one-session mindfulness + TAU

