## **Outcome Measures**

To assess hypothesis 1, subjective experiences of pain intensity, pain unpleasantness, and fatigue will be assessed using the Numerical Rating Scale (NRS) and Visual Analogue Scales (VAS) after surgery, upon discharge. Both intensity (i.e., amount) and unpleasantness of pain will be assessed to capture its sensory and affective dimensions. Two 100-mm visual analog scales (VASs) will be used to assess fatigue and muscle weakness, in line with previous breast cancer trials of post-surgical fatigue (26, 41).

To assess hypothesis 2, we will measure cortisol in hair as a marker of hypothalamus-pituitary-adrenal (HPA) axis activity, and two measures of inflammation – high sensitive CRP

(hs-CRP) and lipopolysaccharide (LPS) reactivity. We consider hs-CRP an acceptable initial marker of systemic inflammation, whilst LPS will provide more nuanced and detailed results of immunological reactivity.

To assess hypothesis 3, NRS will be used to measure post-surgical pain, and FACIT-F (51) to measure post-surgical fatigue at 3 months follow-up. Registry data on pain-related prescriptions will further be extracted from The Norwegian Prescription Database (NorPD).

To assess hypothesis 4, we will use registry data to estimate the number of days participants in each group have been on sick leave (or other welfare benefits) during the year following surgery.

To assess hypothesis 5, we will measure psychological distress by the Hospital Anxiety and Depression Scale (52), as well as data on psychotropic prescriptions from The Norwegian Prescription Database (NorPD).

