## **Interventions**

### *Pre-operative hypnosis*

The pre-operative intervention involves a brief hypnosis intervention that was previously found effective in reducing acute post-surgical pain and fatigue after breast cancer surgery (41). The hypnosis intervention will replicate a previous study of a 15-minute hypnosis intervention (41), and will be provided in a 15-minute session within 1 hour before surgery. The scripted session includes a relaxation-based induction, suggestions for pleasant visual imagery, suggestions to experience relaxation and peace, and specific symptom-focused suggestions. The intervention will be further adapted and modified to the specific context of this study. Trained therapists will hold the session. Patients will be instructed to use hypnosis

on their own following the intervention session. Based on data from the pilot trial, the Norwegian translation and administration of the hypnosis protocol lasts for 20 minutes.

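### Hair cortisol is named as the HPA-axis outcome for Hypothesis 2, but the only itemised schedule takes hair before surgery and never again, so that part of the hypothesis cannot be tested as written

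*Protocol*

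**What the plan says.** Hypothesis 2 (Protocol, Aims and objectives) is a statement about an effect of treatment: "Hypnosis alters markers of bodily stress responses and impacts immune reactivity associated with pain and fatigue".

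Outcome Measures assigns its markers. For the HPA axis, "we will measure cortisol in hair as a marker of" that system's activity; no other HPA marker is named. For inflammation there are two blood measures, hs-CRP and LPS reactivity, of which the protocol says that "LPS will provide more nuanced and detailed results of immunological reactivity".

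Data collection and management gives the sampling schedule. Data are "collected pre-surgery (questionnaires, hair and blood), post-surgery upon discharge (brief phone survey), 3-4 weeks after surgery (blood". It continues: "as well as 3 and 6 months after surgery (only questionnaire data".

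The Pre-operative hypnosis section says that the intervention "will be provided in a 15-minute session within 1 hour before surgery".

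The Abstract describes timing more loosely: "self-reported data and biomarker data will be assessed pre-surgery, post-surgery and 3 and 6 months after surgery". It does not mention hair.

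**The concern.** To show that hypnosis alters a marker, the marker has to be measured at a time when hypnosis could have affected it. The schedule identifies the specimen at each time point, treats hair and blood as separate items, repeats blood at 3-4 weeks and does not repeat hair. It then rules out anything but questionnaires at 3 and 6 months. A second hair sample cannot be read into that text.

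A quantity measured only before treatment is a baseline variable, yet Outcome Measures presents hair cortisol as evidence for a treatment effect. If the text stands, the HPA question goes unanswered although patients give hair for it. There is also a risk of misreading: a null comparison could be taken as evidence against an HPA effect, and a difference as evidence for one, when neither would bear on the question. An analysis plan cannot repair this, because it cannot supply a sample that was not taken.

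**Working it through.** The protocol states sample sizes only for pain and fatigue, and none for hair cortisol or Hypothesis 2, so there is no figure to reproduce. The check is a tabulation of the schedule.

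**Step 1. Specimens by time point (Data collection and management)**

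| Time point | Hair | Blood | Self-report |
|---|---|---|---|
| Pre-surgery | yes | yes | questionnaires |
| Discharge | no | no | brief phone survey |
| 3-4 weeks | no | yes | none listed |
| 3 months | no | no | questionnaires |
| 6 months | no | no | questionnaires |

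Hair: 1 of 5 time points, and 0 of 4 after surgery. Blood: 2 of 5, and 1 of 4 after surgery.

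**Step 2. What can be estimated for hair**

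Let H0 be the pre-surgery hair value, H1 a later one, and A the first-stage arm (hypnosis or mindfulness). The effect of hypnosis on hair cortisol could be estimated from H1 compared between arms, from H1 adjusted for H0, or from H1 - H0. All three need H1, and the schedule contains no H1. Only H0 remains.

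**Step 3. What a comparison of H0 would mean**

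The protocol says hair is taken before surgery, not whether it is taken before or after the session.

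- If hair is taken before the session, H0 cannot depend on what happens in it. By randomisation E[H0 | hypnosis] - E[H0 | mindfulness] = 0, whatever hypnosis does, and an observed difference is chance imbalance.
- If hair is taken after the session, at most about an hour separates the two, because hypnosis falls in the last hour before the operation. The same conclusion then requires that hair cannot register a change in that time. This is an assumption: the protocol gives no time window for hair cortisol.

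The assumption has to cover the control session too, which the protocol times only as before surgery.

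**Step 4. What remains of Hypothesis 2**

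Blood is drawn before surgery and at 3-4 weeks. Provided both assays are run at both draws, hs-CRP and LPS reactivity each have a baseline and a post-intervention value, and the arms can be compared on the latter adjusted for the former. Two of the three named markers are therefore usable.

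**Step 5. The Abstract against the schedule**

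The Abstract's sentence covers self-report and biomarker data together and includes 3 and 6 months. The schedule allows only questionnaires at those times. Both cannot be right for biomarkers. Since the Abstract does not name hair, it does not establish that a later hair sample is planned.

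**The case against.** The strongest reply is that a later hair sample may be intended and that the schedule is the faulty text. The Abstract does speak of biomarkers after surgery, and Figure 1, which belongs in the same section, is not available to this review. This stands to the extent that the sponsor's intention cannot be known from the text. It does not remove the problem: the one section that says when hair is taken lists no later sample, so that section would still need correcting.

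A second reply is that hair cortisol may be meant as a covariate or moderator. That would be a sound use, but the protocol does not say so; it lists hair cortisol as the means of assessing Hypothesis 2.

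Third, it is one marker for a hypothesis that is not primary. That is correct, and it limits the severity.

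A reader might go further and infer any of the following, which the documents do not support:

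- *That a test of hair cortisol has 5% power and that every significant result is a false positive.* The protocol specifies no between-arm test of hair cortisol, its alpha of .05 is stated for the pain and fatigue sample sizes, and the statement depends on the sampling assumption in the working.
- *That Hypothesis 2 as a whole fails.* The inflammation markers keep a post-surgery sample.
- *That the 3-4 week blood values necessarily carry an iACT effect.* The second randomisation is placed after surgery but is not dated relative to that draw.

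**Conclusion.** The point holds for the HPA part of Hypothesis 2. As written there is no post-intervention hair value: hair is listed once before surgery and at none of the four later time points. That follows from the text alone. The further statement, that comparing the pre-surgery values between arms would show only chance baseline imbalance, rests on one assumption: hair is taken before the session, or cannot reflect a change within about an hour.

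One of three markers, for one of five hypotheses, is affected. The hs-CRP and LPS reactivity part stays testable, and pain and fatigue at 3 months are unaffected. Severity is moderate: a named outcome cannot serve its stated purpose, but it is a secondary biomarker and no main conclusion of the trial depends on it.

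The conflict between the Abstract and the schedule over biomarkers at 3 and 6 months is a separate, smaller inconsistency that should be settled at the same time.

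**What to change.** Reconcile the Abstract, Outcome Measures, and Data collection and management so that all three give the same specimens at the same times.

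**If no follow-up hair sample is planned:**

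1. Remove hair cortisol from the outcomes for Hypothesis 2 and state that the pre-surgery value is a baseline covariate or moderator.
2. Test Hypothesis 2 on hs-CRP and LPS reactivity at 3-4 weeks, each adjusted for its own pre-surgery value. State when the second randomisation takes place and, if it precedes that blood draw, include the iACT factor in the model.
3. Limit the wording of Hypothesis 2 to what these markers can show, and correct the biomarker timing in the Abstract.

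This costs wording only: no new procedure, visit or patient.

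**If a follow-up hair sample is already planned:** name its visit in Data collection and management, say why that interval suits hair cortisol, and analyse the follow-up value adjusted for the pre-surgery value and the iACT factor. This too is wording if the sample is already arranged. If it is not, it means an extra sample and assay per patient at a contact in person. That is not assured at 3 and 6 months, since the protocol allows some time points to be answered by electronic link from home. Adding such a sample is the sponsor's choice and is not needed to put the text right.

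In either case, state whether pre-surgery hair is taken before or after the pre-operative session.
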